**Methods/design:**

IIBAPPA is a multi-centre randomised non-inferiority trial. Women with a primary post-partum haemorrhage (PPH) >1000 mL and resultant haemoglobin (Hb) 5.5-8.0 g/dL after resuscitation with ongoing symptomatic anaemia who are otherwise stable (no active bleeding) are eligible to participate. Patients with sepsis or conditions necessitating rapid Hb restoration are excluded. Eligible participants are randomised to receive a blood transfusion or a single dose of intravenous iron polymaltose calculated using the Ganzoni formula. Primary outcome measures include Hb, Ferritin and C-Reactive Protein levels on Day 7. Secondary outcomes evaluate (i) Hb, Ferritin and CRP levels on Day 14, 28, (ii) anaemia symptoms on Day 0, 7, 14 and 28 using structured health related quality of life questionnaires, (iii) treatment safety by assessing adverse reactions and infection endpoints and (iv) the quantitative impact of anaemia on breast feeding quality using a hospital designed questionnaire.

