### Major exclusion criteria

Age < 16 or >50 yearsRefuse consent to blood transfusion or iron infusionCo-morbidities necessitating rapid Hb restoration including: cardiac failure, ischemic heart disease, chronic renal failureKnown hematological malignancyKnown hemaglobinopathies requiring regular transfusionsSepsis (clinical or laboratory evidence—intrapartum fever >38.5 degrees with abnormal vital signs, positive blood culture)Contraindications to iron polymaltose (i.e. asthma, known hypersensitivity to iron polymaltose, chronic polyarthritis, acute renal dysfunction, uncontrolled hyperparathyroidism, infectious hepatitis and iron overload (ferritin >1000 ng/L)Severe symptoms of anemia including dyspnoea at rest, angina pectoris, syncope or transient ischemic attacks.

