### Interventions

All eligible women will be approached and given information about the intervention arms of the study ie. the blood transfusions and intravenous iron including details about the interventions themselves and other scientific and ethical considerations. Those who decline either intervention will be offered oral iron in line with standard practice. These women will be invited to participate in the trial as part of an oral iron subgroup which has an identical follow up protocol. Thse women will be administered 325 mg of oral iron daily. This is not a randomised arm of the study.

Patients in the intervention group will be randomised to receive cross-matched RBC transfusion or an IV iron polymaltose infusion. In patients allocated to RBC transfusion, Hb will be checked after each unit and given to achieve a Hb of at least 9.0 g/dL. Patients who received transfusions will be discharged on 325 mg of oral ferrous sulphate for a minimum of 4 weeks.

Iron poylmaltose was selected instead of iron carboxymaltose as it allows for individualised dose calculations and a larger dose of iron to be administered. Iron carboxymaltose, despite having a shorter infusion time, has a maximum of 1 g that can be administered within a 7 day period.

The dose of iron polymaltose will be calculated according to the Ganzoni formula: Total iron dose (mg) = body weight (kg) x (150-baseline Hb (g/dL)) × 0.24 + 500 mg, assuming a target Hb of 15.0 g/dL which allows for ongoing normal per vaginal loss during the puerperium. For those with Thalassemia minor, the target Hb will be adjusted to reflect the patients pre-pregnancy Hb. Iron will be administered as per hospital protocol which instructs slow infusion at 20-40 mL/h for the first 50 mL, increasing to 120 mL/h based on patient tolerance.

Patients will be pre-medicated with anti-histamine (10 mg cetirizine hydrochloride) and anti-emetic (metoclopramide 10 mg) 1 h prior to the iron infusion to reduce adverse reactions [18]. During the infusion patients will be monitored for adverse affects including itch and urticaria, bronchospasm/dyspnoea, back, joint or muscle pain, nausea, indigestion, abdominal pain, headache, hypotension, tachycardia, syncope, and circulatory collapse [9].

Any patient experiencing an adverse reaction will receive appropriate medical care including additional RBC transfusion if indicated. Infusion rates will be slowed in the instance of mild to moderate reactions and ceased for severe reactions.

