### Statistics

To demonstrate equivalence of the interventions in restoring Hb levels at Day 7 with 90% power at 5% significance (α = 0.025), 116 women need to be recruited to each intervention group. Based on similar studies, this assumes an acceptable difference in Hb of 1 g/dL and an expected difference of 0.7 g/dL [2, 8, 12]. Hence, the final sample size, accounting for a 10% loss to follow up, is a total of 250 women.

Participants experiencing adverse reactions will remain in the trial unless they fail to meet inclusion and exclusion criteria at any point. Data will be analysed according to the intention to treat principle. Primary outcomes and secondary binary outcomes will be analysed using one sided and two group t-tests. The incidence of adverse reactions and symptom scores will be assessed by calculating rates and 95% confidence intervals. Validity of the Post Partum Symptom Scale (PPSS) will be determined at the time of analyses as part of an embedded study and if validated, correlations between subscales and primary outcomes will be analysed.

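### Eligibility is re-applied after randomisation to women with adverse reactions, which conflicts with intention to treat and can cost their later outcome data

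*Protocol article*

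**What the plan says.** Two adjacent sentences in the Statistics section of the protocol article govern this point. The first is a retention rule: "Participants experiencing adverse reactions will remain in the trial unless they fail to meet inclusion and exclusion criteria at any point". The second sets the analysis: "Data will be analysed according to the intention to treat principle". The same section adds: "The incidence of adverse reactions and symptom scores will be assessed by calculating rates and 95% confidence intervals".

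The criteria that the rule refers to are under Participants/eligibility criteria, Major inclusion criteria and Major exclusion criteria. The exclusions include "known hypersensitivity to iron polymaltose", sepsis, acute renal dysfunction, and "Severe symptoms of anemia including dyspnoea at rest, angina pectoris, syncope or transient ischemic attacks". Entry requires a haemoglobin of 5.5 to 8.0 g/dL.

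The events that the trial counts are described elsewhere. The Interventions section says "During the infusion patients will be monitored for adverse affects including itch and urticaria, bronchospasm/dyspnoea", and the list runs on to "hypotension, tachycardia, syncope, and circulatory collapse". The abstract names "treatment safety by assessing adverse reactions and infection endpoints" as a secondary evaluation. The primary outcomes are haemoglobin, ferritin and CRP at Day 7. Symptoms and laboratory values are followed to Day 28.

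**The concern.** Intention to treat keeps every randomised woman in the comparison, in the arm to which she was allocated. A rule that tests eligibility again at any time, and applies it to women who have had a reaction, does the opposite if it is followed. It lets a post-treatment event decide whose Day 7 outcome exists. The article nowhere says that a woman who leaves under this rule is still followed or still analysed.

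The loss would not be random. It is tied to reactions, and one criterion, hypersensitivity to iron polymaltose, can be newly met through study treatment only in the iron arm. Removal could therefore differ between arms. In an open-label non-inferiority trial this can shift the estimated haemoglobin difference relative to the 1 g/dL margin and thin out the later safety data.

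**Working it through.** **1. The rule and the analysis principle.** Iron is given as a single dose. Once a woman has reacted to it, little treatment is left to withdraw from, so remaining in the trial most naturally refers to follow-up and analysis. On that reading the two sentences conflict.

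**2. The criteria against the events counted.**

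| Criterion (Major exclusion criteria or eligibility) | What can trigger it after randomisation | Where the trial counts or expects it |
|---|---|---|
| Known hypersensitivity to iron polymaltose | A reaction to the study iron | Adverse reactions (Interventions, Secondary outcomes) |
| Syncope, dyspnoea at rest | An infusion reaction or severe anaemia | Syncope and dyspnoea are both monitored during infusion |
| Sepsis | Post-partum or treatment-related infection | Infection endpoints (abstract) |
| Acute renal dysfunction | A new complication | Adverse outcomes at follow-up visits |
| Hb 5.5 to 8.0 g/dL | Successful treatment | Transfusion aims for at least 9.0 g/dL (Interventions) |

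The last row shows that the rule cannot be applied as written. A transfused woman who has a reaction and reaches the target no longer meets the entry range. Sites would have to choose which criteria to enforce.

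**3. Reproducing the plan's figure.** The article gives 116 per arm, one-sided alpha 0.025, power 90%, margin 1 g/dL and expected difference 0.7 g/dL. It gives no SD. Solving back:

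SD = (1 − 0.7) × √(116/2) / (1.960 + 1.282) = 0.705 g/dL.

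With an assumed SD of 0.7, the normal formula gives 115 per arm and the t-based calculation 116. The stated figure is therefore consistent with an SD of about 0.7, but that SD is inferred.

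**4. Illustrative effect on type I error.** Let a share f of the iron arm be removed, with true Day 7 Hb D g/dL below the women retained. The iron mean is then overstated by f × D. Holding n at 116 per arm:

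- SE = 0.705 × √(2/116) = 0.0926 g/dL.
- One-sided type I error at the margin = P(Z > 1.96 − f × D / SE).

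D = 1.5 g/dL is assumed. The Background gives iron a serious adverse event risk below 0.5% and a mild risk of 1 to 3%, so f = 0.5% and 3% are the upper ends of those two figures. The value f = 5% is a deliberately high case.

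| f | Shift f × D | Type I error, SD 0.705 | Type I error, SD 1.0 (SE 0.1313) |
|---|---|---|---|
| 0 | 0 | 2.5% | 2.5% |
| 0.5% | 0.0075 | 3.0% | 2.9% |
| 3% | 0.045 | 7.0% | 5.3% |
| 5% | 0.075 | 12.5% | 8.2% |

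The sign depends on D. If the removed women had been given red cells and stood 1.5 g/dL above the rest, 3% removal at SD 0.705 would give P(Z > 1.96 + 0.486) = 0.7%. The bias would then work against iron.

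**5. Power.** With 250 less 10%, 112.5 women per arm are evaluable and power at SD 0.705 is 89.1%. Removing a further 4% gives 87.9%. Lost power is minor; selection related to outcome is the problem.

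**The case against.** The strongest reply is that the retention sentence concerns participation while the next sentence governs analysis, so no data are dropped. Table 1 places the eligibility screen at enrolment only, and the absurd result for transfused women who reach target suggests that the literal reading was not meant. This is a fair account of what may have been intended. It does not cancel a rule that is written to apply at any point, and nothing in the article says that removed women are still followed or analysed.

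Other parts of the reply stand and limit the point:

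- A reader might infer that adverse reactions vanish from the safety count. The documents do not support this. The rule applies to women who have already reacted, reactions are monitored during infusion, and the Data Safety and Monitoring Board reviews their incidence. The triggering event would probably be recorded; later events and outcomes are what is exposed.
- A reader might infer that women whose anaemia simply fails to improve are removed. The sentence covers only women with adverse reactions.
- A reader might infer that the bias must favour iron. Women who react may receive additional red cells under the Interventions section, which would raise their Day 7 Hb, and women who react to transfusion could be removed too.
- The 5% case exceeds the reaction rates quoted in the Background. If those were all severe reactions, it would also exceed the suspension threshold of 2 per 50 (4%).

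**Conclusion.** The point holds as a contradiction between two adjacent sentences, made worse by criteria that overlap the events under study and by a haemoglobin range that treatment is meant to leave behind. It is a stated rule that is wrong as written, not a detail left to the full protocol or analysis plan. What is at risk is the Day 7 to Day 28 haemoglobin, ferritin, CRP, symptom and later safety data of the women removed, possibly unequally by arm.

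The bias can favour non-inferiority, but neither its direction nor its size is established. At the article's own reaction rates, the illustration puts one-sided type I error at about 3% to 7% instead of 2.5%, and 12.5% is reached only in the high case. These figures rest on the back-solved SD, the assumed 1.5 g/dL deficit and removal from the iron arm alone.

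**What to change.** Reconcile the two sentences in the Statistics section. Suggested wording: *Eligibility for the trial and its analysis is determined once, before randomisation. All randomised women are followed to Day 28 and analysed in the arm to which they were allocated, whatever adverse reactions, new exclusion conditions or stopping of study treatment occur. A decision to stop study treatment is separate from follow-up and analysis.*

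How a reaction is managed clinically is outside this point and need not change. The cost is a short replacement text in the protocol, repeated in the analysis plan if there is one. The sample size stays at 116 per arm and no extra visits are needed, because the Day 7, 14 and 28 visits are already scheduled.

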## Design

This is a multi-centre prospective, randomised, open-label, non-inferiority trial.

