### Outcomes

#### Primary outcomes

Hb, ferritn and CRP levels at Day 7

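### Intention to treat is the only stated analysis principle for a non-inferiority claim, although iron-arm women may receive the comparator before Day 7 and a neighbouring sentence lets randomised women be removed

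*Protocol article*

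**What the plan says.** The Design section states: "This is a multi-centre prospective, randomised, open-label, non-inferiority trial". The Primary outcomes section lists "Hb, ferritn and CRP levels at Day 7". The sample size rests on Hb.

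The Statistics section gives one analysis principle: "Data will be analysed according to the intention to treat principle". The sentence before it reads: "Participants experiencing adverse reactions will remain in the trial unless they fail to meet inclusion and exclusion criteria at any point".

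The Interventions section, directly after the paragraph on monitoring the iron infusion, says: "Any patient experiencing an adverse reaction will receive appropriate medical care including additional RBC transfusion if indicated". It adds that the infusion is stopped for severe reactions. The article names no other analysis set and does not say how the analysis treats red cells given to a woman allocated to iron.

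**The concern.** In a superiority trial, crossover to the other arm dilutes the effect, and intention to treat is cautious. In a non-inferiority trial the same dilution helps the claim. Here the treatment an iron-arm woman may receive after a reaction is the comparator itself, and it acts directly on the primary endpoint. Her Day 7 Hb reflects iron plus red cells, or mostly red cells if the infusion was stopped. Treating staff know the allocation, so giving red cells is not protected from that knowledge.

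The removal clause adds a second route to the same bias. The exclusion criteria include severe anaemia symptoms such as syncope. Read literally, an iron-arm woman who has a reaction and then meets such a criterion could leave the trial. So she may be either counted with a raised Hb or not counted at all, and both can favour iron.

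At stake is the conclusion drawn in the Discussion, that iron is an alternative to transfusion. It would rest partly on women who were transfused or removed.

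**Working it through.** **1. Inputs.** From the Statistics section: "with 90% power at 5% significance (α = 0.025), 116 women need to be recruited to each intervention group", and "this assumes an acceptable difference in Hb of 1 g/dL and an expected difference of 0.7 g/dL". I take 0.025 as one-sided. From the Background: for newer iron preparations, serious adverse events below 0.5% and mild ones 1–3%. Added together, these give at most about 3.5%. No standard deviation (SD) and no transfusion rate in the iron arm are stated.

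**2. The plan's own figure.** Without an SD, 116 per arm cannot be reproduced from the stated inputs. Back-solving from n = 2·SD²·(1.960 + 1.282)² / (1 − 0.7)² gives SD = 0.3 × √58 / 3.242 = 0.705 g/dL. I use 0.705 as the implied value, with 1.0 and 1.5 as assumed alternatives.

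**3. Direction.** Let d be the Hb deficit of iron against red cells with no crossover, and f the share of iron-arm women given red cells. Assume that these women reach the red-cell-arm mean. The intention-to-treat difference is then d(1 − f), which is smaller than d whenever f > 0.

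**4. Size at the margin.** With SE = SD × √(2/116), the chance of declaring non-inferiority is Φ((1 − d(1 − f))/SE − 1.96). At d = 1 this becomes Φ(f/SE − 1.96). SE is 0.0926, 0.1313 and 0.197 for the three SDs. For f = 3.5% and SD 0.705: 0.035/0.0926 = 0.378, and Φ(0.378 − 1.96) = 5.7%.

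| Share of iron arm given red cells | SD 0.705 | SD 1.0 | SD 1.5 |
|---|---|---|---|
| 0 | 2.5% | 2.5% | 2.5% |
| 0.5% (serious reactions only) | 2.8% | 2.7% | 2.7% |
| 3% | 5.1% | 4.2% | 3.5% |
| 3.5% (every quoted reaction) | 5.7% | 4.5% | 3.7% |
| 5% (illustrative) | 7.8% | 5.7% | 4.4% |
| 10% (illustrative) | 19.0% | 11.5% | 7.3% |
| 15% (illustrative) | 36.7% | 20.7% | 11.5% |

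At the planned difference of 0.7 g/dL and SD 0.705, f = 3.5% moves the difference to 0.7 × 0.965 = 0.676 and power from 90% to 94%.

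**5. A tempting remedy, checked.** One could replace the Day 7 value of each transfused iron-arm woman by her last Hb before transfusion and require non-inferiority in that analysis too. Table 1 schedules no Hb between enrolment and Day 7, so that value would usually be baseline. The Background cites an average rise of 2.5 g/dL by day 5 after iron, so take a penalty of 2.5 g/dL per woman.

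- At 3% transfused, the difference becomes 0.7 + 0.03 × 2.5 = 0.775, and power is Φ(0.225/0.0926 − 1.96) = 68%.
- At 5%, it becomes 0.825, and power is Φ(0.175/0.0926 − 1.96) = 47%.
- The substitution also adds variance of f(1 − f) × 2.5² in the iron arm. Counting it, power is about 61% and 38%.

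**6. The two adjacent sentences.** One analyses women as randomised. The other drops some of them for events after randomisation. Both cannot define the same analysis set.

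**The case against.** Intention to treat is a legitimate treatment-policy analysis. It answers what happens when iron is offered and red cells remain available. The text states a principle and does not rule out supporting analyses. The article is condensed and the statistical analysis plan is not shown, so the absence of a per-protocol set is not an error in itself. This stands, and it limits the point to an improvement.

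The effect may also be small. The article mentions red cells outside the allocated treatment only as care for an adverse reaction. Few mild reactions would plausibly lead to transfusion, so 3.5% is generous against the quoted rates. The permission covers any patient, so women in the red cell arm might also receive extra cells, which would push the other way. The calculation does not net this off.

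A reader might infer more: that women in whom iron failed to raise Hb would be transfused and then credited to iron. The documents do not support that. They contain no provision for transfusing an iron-arm woman because of a poor Hb response, and Table 1 has no Hb before Day 7 to reveal one. A higher rate of red cell use in the iron arm because the trial is open-label is likewise an inference.

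The objection leaves two things standing: the direction of the bias, and the removal clause, which is a contradiction on the page.

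**Conclusion.** The point holds as a cheap improvement. Red cells given in the iron arm before Day 7 bias the intention-to-treat comparison towards non-inferiority, and nothing in the article measures or corrects this. At the quoted reaction rates the one-sided error at the margin rises from 2.5% to about 4–6%. That assumes every quoted reaction leads to transfusion, transfused women reach the red-cell-arm mean, 116 women per arm are analysed, and the SD lies between 0.7 and 1.5 g/dL.

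A reader might take the 19% or 37% in the table as the expected error. Those figures need 10% or 15% of the iron arm to be transfused, rates with no source in the documents, and an SD that is only back-solved. They show sensitivity and are not an estimate.

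The conflict between intention to treat and the removal clause depends on none of these assumptions and must be reconciled.

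**What to change.** Keep intention to treat as the primary analysis and add the following to the Statistics section.

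- **Analysis set.** All randomised women stay in the intention-to-treat set. Events after randomisation, including later failure of an entry criterion, do not remove a woman from it. Reword the removal sentence to agree.
- **Data.** Record the date and number of units of any red cells given outside the allocated treatment, and report them by arm. The Data collection section describes recording blood units for the allocated intervention only.
- **Supporting analyses.** Prespecify a per-protocol analysis. It is not enough alone, because dropping transfused iron-arm women may remove the poorest responders. Also prespecify a sensitivity analysis for iron-arm women transfused before Day 7, such as imputation under a hypothetical strategy or a delta-adjusted tipping-point analysis. Show the last pre-transfusion or baseline Hb only as a worst-case bound.
- **Interpretation.** Describe non-inferiority as robust only if these analyses are consistent with it. Do not make baseline substitution a formal gate, given the power loss shown above.

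No change to clinical management is needed. The cost is a little more data capture and analysis, and a more cautious conclusion if crossover proves common.

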### Procedures, recruitment and randomisation

Table 1 describes the schedule of enrolment, interventions and assessments during the trial.

**Table 1 Tab1:** Schedule for enrolment, interventions and assessments

	Enrolment	Allocation	Post Allocation				Close-out
TIMEPOINT	Feb 2016	At Enrolment	0-48 h	Day 7	Day14	Day 28	Day 28
ENROLMENT:							
Eligibility screen	X						
Informed consent	X						
Randomisation		X					
Intervention/Preparation (pharmacy/blood bank)			X				
INTERVENTIONS:							
RBC Transfusion			X				
Intravenous Iron Polymaltose			X				
ASSESSMENTS:							
E-5D,MFI-20) and PPSS symptom scores			X	X	X	X	
Clinical history and examination	X		X	X	X	X	
Hb	X			X	X	X	
Ferritin	X			X	X	X	
UEC	X						
CRP	X			X	X	X	
Reticulocyte Count	X			X	X	X	
Group and hold	X						
Vital Signs		X		X	X	X	

Clinical staff at all sites will be able to contact the research team at any time to enrol participants. Research midwives at the primary site will identify women from daily birth records who have had a PPH >1000mls. These women will be briefed on the study using a structured information sheet about the trial and interventions. Following this they will verbally consent to preliminary bloods including a group and hold, haemoglobin, creatinine (to exclude acute kidney injury), ferritin and CRP. Eligible patients will then provide written informed consent and be enrolled to participate in the study (intervention and follow up phases).

Participants will be stratified as per mode of delivery and randomisation will occur within these groups by a computer generated list, blocked in a 1:1 ratio to each intervention. A central telephone service will be accessed to allocate the intervention and study identification number.

Eligible women who decline partipation in the trial will be offered 325 mg oral ferrous sulphate daily until iron replete, which is in accordance with current standard practice guidelines. This will be mentioned in the consent process.

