### Data collection

Each participant will have a study file labelled with their name, medical record number, study identification number and allocated treatment. This will contain copies of their consent forms (the original will remain in their hospital file while they are an inpatient), questionnaires and comprehensive study checklists template for documenting outcome variables and other clinical data. Files will be kept in locked cabinets on the ward and in the principle researcher’s office after discharge and remain on site for 7 years before being destroyed/archived.

Baseline blood results (Hb, ferritin, CRP) for all enrolled participants will be manually transcribed by researchers from the hospital electronic database into the participant’s study file. Once allocated to an intervention, the number and coding sticker of each blood unit or the serial number and dose of the pre-packaged iron infusion will be recorded in the template.

Patient symptoms will be scored on Day 0 prior to receiving any intervention using previously validated HRQoL questionnaires: the EuroQol-5D (E-5D), the Multidimensional Fatigue Inventory (MFI-20) and our in-hospital devised Post-Partum Symptom Score (PPSS).

The EQ-5D measures a patient’s activity level and emotional attitude at a single point in time, indirectly reflecting symptom severity. It consists of five items (Mobility, Self-Care, Usual Activities, Pain/Discomfort and Anxiety/Depression) where a patient scores: 1 = no problems, 2 = more problems, 3 = extreme problems. The sixth item is a patient’s own global evaluation of their health using a visual analogue scale with a range from 0 (worst imaginable health state) to 100 (best imaginable health state) [21].

The MFI is a 20-item self-report instrument designed to comprehensively measure fatigue. It evaluates: general, physical and mental fatigue and reduced motivation and activity. Patients score each dimension on a scale ranging from 4 to 20 where 4 is optimal. Hence, higher scores indicate more severe symptoms. Scales are balanced to reduce the influence of response tendencies. Each scale sub-total is interpreted independently. Questions are structured to evaluate symptoms over a period of time (5-7 days) which is particularly useful to measure treatment impacts [22]. Both the MFI and EQ-5D have previously been validated in pilot studies of obstetric cohorts [23].

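### The primary t-test of Day 7 Hb uses neither baseline Hb nor the mode-of-delivery strata: it is valid, but gives up some precision at no saving

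*Protocol article*

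**What the plan says.** Under Primary outcomes the article lists "Hb, ferritn and CRP levels at Day 7". These are levels, not changes from baseline. The Statistics section names the test: "Primary outcomes and secondary binary outcomes will be analysed using one sided and two group t-tests". No covariate, change score or stratum term appears anywhere in the article.

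Under Procedures, recruitment and randomisation, "Participants will be stratified as per mode of delivery and randomisation will occur within these groups", with blocked 1:1 allocation. Under Data collection, "Baseline blood results (Hb, ferritin, CRP) for all enrolled participants will be manually transcribed by researchers". Table 1 also places Hb, ferritin and CRP at enrolment.

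The sample size is set on Day 7 Hb, "with 90% power at 5% significance (α = 0.025), 116 women need to be recruited to each intervention group". On the margin, "this assumes an acceptable difference in Hb of 1 g/dL", with an expected difference of 0.7 g/dL. After an allowance of 10% for loss to follow-up, the total is given as 250.

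**The concern.** The design controls for mode of delivery at randomisation and measures Hb before treatment, but the stated analysis uses neither. Two consequences follow.

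- Stratified allocation balances mode of delivery between the arms. A pooled two-group standard error does not credit that balance, so it is somewhat too large if mode of delivery predicts Day 7 Hb.
- Any part of Day 7 Hb that baseline Hb predicts stays in the error term.

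Precision matters in this trial because the expected difference (0.7) lies only 1.0 − 0.7 = 0.3 g/dL inside the margin. The sample size also has no slack, since 10% loss from 250 leaves fewer than 116 per arm. An SAP may exist and is not shown. The point is raised because the article itself names the test and does not leave the choice open.

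**Working it through.** **Inputs from the article.** Margin 1 g/dL; expected difference 0.7 g/dL, taken as iron being lower; α = 0.025, read as one-sided; 90% power; 116 per arm; 250 in total with 10% loss.

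**Inputs the article does not give (assumptions).** The SD of Day 7 Hb, the correlation ρ between baseline and Day 7 Hb, and the share R² of variance in Day 7 Hb explained by mode of delivery.

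**Step 1: the plan's own figure.** Without an SD, 116 cannot be reproduced from stated inputs alone, so it is solved backwards. From n = 2·SD²·(1.960 + 1.282)²/(1.0 − 0.7)²,

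SD = 0.3 × √(116/2) / 3.242 = 0.705 g/dL.

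Forwards with SD 0.7, the normal approximation gives 115 per arm. The t-test (noncentral t) needs 116, with power 90.2%. So 116 agrees with an unadjusted t-test at an SD of about 0.7, and that value is used below. Other readings imply other SDs: 0.78 if α is one-sided 0.05, and 2.35 if the true difference is taken as zero.

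**Step 2: adjusting for baseline Hb.** The residual SD under ANCOVA is 0.7 × √(1 − ρ²). Noncentral-t power, distance to margin 0.3, one-sided 0.025:

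| ρ (assumed) | Residual variance, 1 − ρ² | n per arm for 90% (normal approx.) | Power, 116 per arm | Power, 112 per arm |
|---|---|---|---|---|
| 0 (t-test) | 1.00 | 115 | 90.2% | 89.1% |
| 0.1 | 0.99 | 114 | 90.4% | 89.4% |
| 0.2 | 0.96 | 110 | 91.3% | 90.3% |
| 0.3 | 0.91 | 105 | 92.6% | 91.7% |
| 0.5 | 0.75 | 86 | 96.4% | 95.8% |

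The 112 column is 250 × 0.9 = 225, or 112 complete pairs. The variance ratio 1 − ρ² does not depend on the SD; the power figures do.

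**Step 3: which ρ is plausible.** Three design features may hold it down: entry Hb is confined to 5.5–8.0 g/dL, transfusion is titrated to a target Hb, and the iron dose is calculated from baseline Hb. If entry Hb were uniform over that window (assumption), its SD would be 2.5/√12 = 0.72. The slope of Day 7 Hb on baseline would then be ρ × 0.7/0.72: about 0.19 for ρ = 0.2, 0.29 for ρ = 0.3 and 0.49 for ρ = 0.5. At ρ = 0.5, about half of a woman's entry difference would have to persist to Day 7.

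**Step 4: adjusting for the strata alone.** If mode of delivery explains 1%, 2%, 5% or 10% of the variance (assumption), power at 116 per arm with a residual SD of 0.7 × √(1 − R²) is 90.4%, 90.7%, 91.5% or 92.9%.

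**Step 5: validity.** With the strata balanced by design, the t-test's standard error is too large by a factor of about 1/√(1 − R²). Its effective critical value is 1.960/√(1 − R²): 1.980, 2.011 and 2.066 for R² of 2%, 5% and 10%. The one-sided error is then about 2.4%, 2.2% and 1.9% instead of 2.5%. A simulation agrees (8,000 runs per setting, 116 per arm, two equal strata, SD 0.7):

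| ρ, R² | Error at margin: t-test | Error at margin: adjusted | Power: t-test | Power: adjusted |
|---|---|---|---|---|
| 0.3, 2% | 2.3% | 2.3% | 90.5% | 93.1% |
| 0.5, 5% | 2.1% | 2.3% | 90.7% | 97.1% |
| 0.5, 10% | 2.0% | 2.4% | 91.7% | 98.2% |

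**The case against.** The strongest reply is that nothing here is wrong. A two-group t-test is a valid analysis of a randomised comparison. Ignoring the strata can only make it conservative, so it cannot create a false claim of non-inferiority. With the implied SD, 116 per arm delivers the planned power for this very test. Adjustment therefore adds power beyond the plan and does not repair a shortfall in it. Covariates are also commonly left to an SAP. Most of this stands, and it limits the point to efficiency. It does not remove the point: the article commits to a named unadjusted test, and the better one needs no new data.

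A reader might infer three stronger things that the documents do not support.

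- **That the analysis endangers the trial's conclusion.** The error rates in Step 5 show otherwise.
- **That the gain is large.** At SD 0.9 with correlations of 0.3–0.6, power would go from 71.5% to 75.5–88.5%. But SD 0.9 does not match 116 per arm at 90% power, and that range leaves out the low correlations that the entry window, titration and baseline-based dosing make plausible.
- **That raw-scale t-tests of ferritin and CRP are mistaken because those variables are skewed.** The article says nothing about their distributions, and with about 116 per arm moderate skew need not invalidate a comparison of means.

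**Conclusion.** The point holds as a loss of efficiency, not of validity. The article fixes an unadjusted t-test for Day 7 Hb while stratifying by mode of delivery and recording baseline Hb for everyone.

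At an assumed SD of 0.7, with correlations of 0.1 to 0.3, the gain from baseline adjustment at 116 per arm is 0.2 to 2.4 percentage points of power (90.4% − 90.2% and 92.6% − 90.2%). At a correlation of 0.5 it is 6.2 points (96.4% − 90.2%). The low end may well be the realistic one. The practical value is clearest at 112 per arm, where the t-test falls just under the planned 90% and a correlation of only 0.2 brings it back. These sizes rest on an SD and a correlation that the article does not state, so the direction of the gain is firmer than its amount.

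**What to change.** Before unblinded data are seen, name as the primary analysis an ANCOVA of Day 7 Hb on arm, baseline Hb and mode of delivery. Report the adjusted difference with its two-sided 95% confidence interval. Conclude non-inferiority if the lower limit for iron minus transfusion lies above −1 g/dL. Keep the unadjusted t-test as a sensitivity analysis.

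Analyse Day 7 ferritin and CRP in the same way, each adjusted for its own baseline value and mode of delivery. Log transformation is a secondary suggestion, to be used only if the data prove skewed.

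The cost is wording. All covariates are already collected, no visit or sample is added, and with more than 200 women a few model terms cost almost no degrees of freedom. Timing matters because the trial is open-label: adjustment chosen after results are known would look selective.
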